### Sample size

For a feasibility study, it is inappropriate to calculate sample size based on desired statistical power to detect a treatment effect,^35^ because the primary aim of the study is to assess if a full trial can or should be conducted. Feasibility outcomes are descriptive in nature; therefore, inferential statistics regarding treatment effects will not be computed. To achieve the primary objectives related to feasibility outcomes, the research team estimated that 40 participants would be adequate.^36^ Twenty patients will be randomly allocated to each treatment condition.

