#### Dosage of the PEG intervention

A single approximately 1 hour pain education will be delivered to the PEG, because evidence indicates that: (1) interventions as brief as 5 min have been shown to have reassuring effects lasting for up to a year,^44^ and a single consultation has been found to be as reassuring as the multiple session interventions.^47^ We prefer a single session treatment over multiple session treatment, because for many patients in rural Nepal, it is difficult to deliver a multiple session treatment in reality. Thus, we plan to provide a single session delivering key concepts of Explain Pain, which will be reinforced by providing patient handouts to look at and read at home. In fact, a 1-hour session should be adequate to cover the key Explain Pain concepts by keeping the content simple and jargon free. Use of a plain language in the health-related education is important to adapt in low health literacy.^48^

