9	Satisfaction of treatment	All the participants in both the conditions will be asked to respond to the Patient Global Assessment of Treatment Satisfaction scale at 1 week following treatment.^65 66^ The question asked will be, ‘*How satisfied are you overall with the study treatment?*’ Responses to this question are made on a five-point categorical scale (0=‘*Very dissatisfied*’; 1=‘*Dissatisfied*’; 2=‘*Neutral or no preference’*; 3= ‘*Satisfied*’; 4=‘*Very satisfied*’).	Mean treatment satisfaction scores will be computed for each treatment condition separately. Between-condition differences will be evaluated using a t-test.
10	Difficulty in understanding the information provided by the physiotherapist.	All the participants will be asked about the difficulty in understanding the information provided by the physiotherapist. The question asked will be, ‘*How difficult was it for you to understand* the *information provided by the physiotherapist?*’ Responses will be provided on a 5-point Likert scale, where 1=‘*Very easy*’, 2=‘*Easy*’, 3=‘*Neither easy nor difficult*’, 4=‘*Difficult*’, 5=‘*Very difficult*’.	The differences in the difficulty in understanding the information provided will be compared between the two groups.
11	Difficulty in understanding the instructions for what to do.	All participants will be asked about the difficulty in understanding the instructions provided by the physiotherapist for what to do at home. The question asked will be, ‘*How difficult was it for you to understand the instructions provided by the physiotherapist for what to do at home?*’ using a on a 5-point Likert scale, where 1=‘Very easy’, 2=‘*Easy*’, 3=‘*Neither easy nor difficult*’, 4=‘*Difficult*’, 5=‘*Very difficult*’.	Frequencies and rates of each response category will be computed for each group separately.
12	Adverse events	All participants will be asked about any adverse events after treatment. All responses will be recorded verbatim.	The number of adverse events listed will be computed for each treatment condition separately. The responses will be analysed qualitatively (see text).

LBP, low back pain.

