Score on the credibility of treatment scale	Control condition is >0.50 SD credible than pain education group.	Develop a new control condition for the EP trial and pilot test to ensure that its credibility rating is <0.50 SD different from pain education group.	-	The credibility scores of the two conditions are within 0.50 SD units of each other.
Adherence to treatment	<50% attend the treatment session after randomisation.	Identify reasons for not attending the treatment session in order to increase attendance in the full trial.	50%–80% of the participants attend the treatment session.	80% or more of the participants attend the treatment sessions.
Difficulty scale	If ≥50% participants in the experimental group rate pain education as very difficult, very easy, easy or neither easy nor difficult.	Make the intervention a little more challenging if more than half of the participants report 1–3 out of 5 in the difficulty scale, by increasing the depth of the education, by adding more pain biology education content. Whereas if more than half participants report the intervention as very difficult, reduce the complexity. Re-evaluate complexity in a second cohort of at least five participants to ensure appropriate level of difficulty.	-	≥50% participants in the experimental group rate pain education as a ‘difficult’ intervention (4 out of 5 in the difficulty scale). This is the preferred difficulty level because we want pain education intervention to be difficult enough to challenge participants but not too easy or very difficult.

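### The difficulty criterion in Table 4 uses a comprehension question to judge whether the education is challenging enough, and its modify and proceed rules overlap and leave a gap

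*Protocol article*

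**What the plan says.** Difficulty in understanding the intervention is the ninth primary objective (Aims and objectives). Table 2 measures it with two items. For item 10, "All the participants will be asked about the difficulty in understanding the information provided by the physiotherapist"; item 11 concerns the instructions for what to do at home. Both open with the words "How difficult was it for you to understand" and use a scale from 1 (very easy) to 5 (very difficult), on which 4 is 'difficult'.

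Table 4 (Criteria for feasibility) has one row called the difficulty scale. The protocol is to be modified "If ≥50% participants in the experimental group rate pain education as very difficult, very easy, easy or neither easy nor difficult". No close monitoring is needed when "≥50% participants in the experimental group rate pain education as a ‘difficult’ intervention (4 out of 5 in the difficulty scale". There is no intermediate band. The same cell gives the reason: the team prefers education that challenges participants without being too easy or very hard. The action cell says to add depth and pain biology content if more than half answer 1 to 3, to reduce complexity if more than half answer 'very difficult', and to re-evaluate in a second cohort of at least five.

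Dosage of the PEG intervention says one hour should be enough to cover the key concepts by "keeping the content simple and jargon free", and stresses plain language for low health literacy. Participant screening and recruitment deliberately includes people who cannot read or sign. Home advice for PEG group plans many more images than text.

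On numbers, Sample size says "the research team estimated that 40 participants would be adequate" and "Twenty patients will be randomly allocated to each treatment condition".

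**The concern.** The row is meant to judge whether the education is demanding enough, but the answers it scores report whether people could follow it. Being challenged by an idea and struggling to understand an explanation are different things, and neither Table 2 item captures the first. Handouts that achieve the plain-language aim would tend to draw answers of 1 to 3. Table 4 reads those answers as a reason to add content, under a column saying that the full trial is not feasible as designed. Material that every participant found hard to understand can satisfy the proceed rule.

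The rule also does not work as a decision rule, whatever one thinks of the rationale. Its two thresholds overlap, and its trigger pools answers from opposite ends of the scale while its actions are directional. Since Table 4 informs the decision on the full trial, the team could face a result that the table answers twice, or answers without saying what to change.

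**Working it through.** The plan derives no figure for this criterion: 40 is the team's estimate and 50% is a set threshold. There is nothing to reproduce, so the check is of how the rule behaves.

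**Inputs.** Pain education group n = 20 (Sample size). Let a be the number answering 1 to 3, c the number answering 4, and b the number answering 5, with a + b + c = 20. Table 4 then reads:
- modify if a + b ≥ 10;
- proceed without close monitoring if c ≥ 10;
- add content if a > 10;
- reduce complexity if b > 10.

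**Which item.** Table 4 does not name it. Item 10 asks about the information, which fits the wording about pain education, but its planned analysis is a between-group comparison. Item 11 asks about home instructions, and it is the one whose planned analysis gives response frequencies per group, the quantity Table 4 needs. Both ask about understanding, so the mismatch with the rationale holds either way.

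**Hard material passes.** Take c = 11, b = 9, a = 0. The modify trigger is 9/20 = 45%, not met. The proceed rule is 11/20 = 55%, met. All 20 found it difficult or very difficult to understand, and the row asks for neither modification nor close monitoring.

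**Overlap.** If c = 10, then a + b = 10, so both rules are met at 50%. Neither a nor b can then exceed 10, so no directional action applies either. The probability of this result is C(20,10) p^10 (1 − p)^10, where p is the true share answering 4:
- p = 0.20: 0.002
- p = 0.40: 0.117
- p = 0.50: 184,756 / 1,048,576 = 0.176

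**No direction.** Take b = 5, a = 6, c = 9. The trigger is 11/20 = 55%, met. But a = 6 (30%) and b = 5 (25%), so neither exceeds half. The protocol must be modified, and the row does not say which way.

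**Chance of passing.** The documents give no expected p, so it is assumed over a range. P(pass) = Σ C(n,x) p^x (1 − p)^(n − x), summed from the smallest x that is at least half of n. The items are collected at the final assessment, so n = 17 and n = 14 (15% and 30% drop-out) are shown as well.

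| Assumed p | n = 20 (≥10) | n = 17 (≥9) | n = 14 (≥7) |
|---|---|---|---|
| 0.20 | 0.003 | 0.003 | 0.012 |
| 0.30 | 0.048 | 0.040 | 0.093 |
| 0.40 | 0.245 | 0.199 | 0.308 |
| 0.50 | 0.588 | 0.500 | 0.605 |
| 0.60 | 0.873 | 0.801 | 0.850 |

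Of the shares shown, passing is at least an even chance only once half or more answer exactly 'difficult'.

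**The case against.** The rule is deliberate. Table 4 states the preferred level and the reason for it, so this is not a slip. Plain words can carry demanding ideas, so simple language and conceptual depth can coexist. That stands, and it is why the conflict with the plain-language aim is a tension and not a flat contradiction. It does not rescue the measure, because both items ask about understanding and neither asks about challenge.

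A reader might infer that well-understood material is almost certain to fail. The documents do not support this without an assumed response rate. It holds for shares up to about 30% with 20 participants, but at 40% the chance of passing is about one in four.

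A reader might also infer that failing this row stops the full trial. It does not: the column says not feasible as designed, and the consequence is a modified protocol with a re-check in a second cohort. Nor would hard material necessarily reach the full trial unchanged. This is one row of eight, the handouts are pretested in 5 to 10 people, and Pain education group says any modifications required will be made.

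The overlap needs an even number of respondents and has a probability of at most 0.176 with 20. The 5/6/9 split is an unusual pattern, and the re-evaluation step could be read as applying to it. What is missing there is the direction of change. These points limit how often the faults would show, but the rule remains wrong as written.

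**Conclusion.** The concern holds as a mismatch between measure and purpose, together with a faulty decision rule. Three parts follow from the text alone and need no assumption: comprehension items are used to judge challenge, with the scored item unnamed; results such as 11 'difficult' and 9 'very difficult' pass; and the thresholds overlap at 10 of 20 and leave some modify results without a direction. The size of the effect on passing depends on a share that the protocol does not give. With 20 respondents, assumed shares of 20%, 30%, 40% and 50% give passing chances of 0.3%, 4.8%, 24.5% and 58.8%. The row should be corrected before it is used to inform the full trial, but it does not threaten the feasibility trial itself.

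**What to change.** - Name the Table 2 item that Table 4 scores, and plan its response frequencies for the pain education group.
- Judge the comprehension items as comprehension: prespecify a share of answers 4 or 5 that triggers simplification. Choose that share with n = 20 in mind. Simply reversing the rule at 50% would flag material that 30% or 40% find hard only 4.8% or 24.5% of the time.
- If conceptual challenge is wanted, ask about it in a separate one-line question with its own acceptable band. This keeps the team's aim.
- Split the modify trigger into two directional rules, each using the same threshold as its action, and state what happens when neither is met.
- Make the modify and proceed cut-offs mutually exclusive, for example by using a strict inequality on one side.

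The cost is rewording one row of Table 4 and at most one added question at the final assessment. Sample size and other procedures are unaffected.

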### Limitation of the study

As this is a feasibility study, the results of the current study will not provide findings regarding the efficacy of the interventions being tested. The study will only evaluate if this research study is viable as a full trial and inform any recommendations for modification of the protocols for the full trial resulting from the findings of this feasibility trial.

### Plan for supervision and monitoring

The study will be conducted and monitored by the lead investigator under the supervision of the coauthors ([name] and [name]), with assistance from research assistant(s). All the ethical principles as provided by Declaration of Helsinki will be followed by all the members of this research throughout the study. The investigators will not violate any of the rules and ethical principles of NHRC. Monitoring for the NHRC ethical principles will be regulated by the primary investigator and followed by all researchers and research assistants involved in the study.

### Plan for data integrity and management

The research data will be collected by a research assistant who will be trained to collect the research data and manage the data by compiling in a file for individual patient. Participant identifiers (including name, address and contact information) will be removed from the research data and will be stored separately. Data will be entered in Microsoft Excel. Identification of the groups as intervention and CG will be removed from the excel sheet. Research data will be monitored weekly by scrutinising entered data. Any errors in entry will be identified (if any) and amended. Consent forms will be scanned and stored in password-protected computers of the lead researcher and at the University of Otago along with other research data files.

### Data analysis plan

Descriptive statistics will be computed to describe the baseline and demographic characteristics of the study participants. As it is a feasibility study, level of significance and hypothesis testing regarding treatment efficacy will not be performed. Effect sizes representing between-group differences in change in the primary and secondary outcomes will be computed, but these effect sizes will not be considered as a criteria for sample size estimation for the full trial, nor as a criteria to proceed to the full trial, because of the inadequate power of the current feasibility study. Treatment effects for the secondary outcome measures will be presented as means, SD and CIs of the means. Difference between the mean scores of each secondary outcome will be compared with the minimum important change (MIC) values of the outcome measures, if the MIC scores are available. The analysis plans of the primary feasibility objectives are described in table 2.

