7	Credibility and acceptability of the interventions	Treatment credibility will be assessed using five questions adapted from Borkovec and Nau.^63^ The questions will be modified to fit ‘Pain education’ and ‘Control group’ as a treatment for patients with LBP and will be administered to all the participants in both conditions. One, important cultural adaptation for the scoring will be made by changing the numerical scale proposed by Borkovec and Nau to a Verbal Rating Scale, because Numerical Rating Scales have been shown to be unsuitable in Nepalese with musculoskeletal pain, especially in those who are older and have low educational attainment.^64^ Responses for each of the five questions will be recorded on a Likert scale where, 0=‘*Not at all*’, 1=‘*A little bit*’, 2=‘*Somewhat*’, 3=‘*Quite a bit*’, 4=‘*Very much*’. The questions are: 1. How logical does the treatment provided seem to you for the management of low back pain? 2. How confident would you be that this treatment would be successful in reducing pain? 3. How confident would you be in recommending this treatment to a friend or family who also has LBP? 4. If you were having low back pain again, would you be willing to undergo such treatment? 5. How successful do you feel this treatment would be in reducing pain in other parts of the body, for example, knee pain? All the questions will be asked at baseline and at 1 week following treatment.	Mean of the total scores on the credibility scale will be computed separately for each condition. Between-condition differences in creditability will be evaluated using a t-test.
8	Adherence to the intervention	Adherence to treatment will be assessed by asking the participants in both conditions to maintain a record of daily home treatment that was followed by every participant. The participants will tick mark a box for every day for a total of 5 days between the two assessment time-points to indicate their adherence to prescribed home exercise programme. Additionally, participants will be requested to record any deviation of prescribed home treatment programme (eg, additional visit to the clinic and use of other interventions). Finally, question regarding non-adherence will be asked.	The total number of treatment adherence days will be summed for each treatment condition separately. Deviation from the treatment protocol will be recorded. Finally, the reasons for non-adherence will also be listed.

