Pain catastrophising	Pain Catastrophizing Scale (PCS)^55^	13	5-point, ordinal	Respondents are asked to indicate the degree or frequency with which they have each catastrophising response listed when they ‘… are experiencing pain’ on a 5-point Likert scale (0=‘*Not at all*’, 1=‘*To a slight degree*’, 2=‘*To a moderate degree*’, 3=‘*To a great degree*’ and 4=‘*All the time*’). The total PCS score can range from 0 to 52, with higher scores representing higher pain catastrophising.	Good to excellent internal consistencies: Cronbach’s alpha=0.85–0.93. Excellent test–retest stability (ICC=0.89–0.90). Positive moderate correlations with measures of pain intensity, depression and anxiety in a sample of individuals with chronic pain from Nepal.^55^
Patient’s global rating of change	Global Rating of Change^57 66 67^	1	1–7, ordinal	Respondents are asked to rate their ‘*overall improvement*’ their health condition since the study enrolment. Responses can range from 1 to 7 with 4=‘*No change*’. Scores greater than 4 indicate greater improvement and scores lower than 4 indicate a perceived worsening in the respondent’s health condition.	MIC: 1 point change.^57 58^
Quality of life (QOL)	QOL rating scale	2	5-point, ordinal	Respondents are asked to rate their general QOL and general health by responding to the questions: •‘*In general, how would you rate your overall quality of life during the past week?*’ •‘*How would you rate your general health during the past week?*’ The response options are: 1=‘Very bad’, 2=‘Bad’, 3=‘Fair’, 4=‘Good’ and 5=‘Very good’.^68^ Greater score indicate better QOL.	Not available during the time of protocol writing the study protocol.
Pain intensity	PROMIS Pain Intensity short-form 3b^54^	3	5-point, ordinal	Respondents are asked to rate their current pain and their worst and average pain intensity in past 7 days on 5-point Likert scales (1=‘*Had no Pain*’, 2=‘*Mild*’, 3=‘*Moderate*’, 4=‘*Severe*’, and 5=‘*Very severe*’). Responses are scored as a T-score that can range from 0 to 100, with a mean of 50 and SD of 10 in the normative sample.	Good test–retest reliability (ICC=0.71) in a sample of individuals with chronic pain from Nepal.^54^

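### The effect-size sentence asks for change in all primary and secondary outcomes, which fits only those measured twice; for the seven secondary scales with a baseline, a baseline-adjusted contrast would be somewhat more precise

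*Protocol article*

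**What the plan says.** The Data analysis plan of the protocol article gives one definition: "Effect sizes representing between-group differences in change in the primary and secondary outcomes will be computed". It names no exception. The sentence goes on to limit the use of these figures: "these effect sizes will not be considered as a criteria for sample size estimation for the full trial", and they are likewise excluded from the decision to proceed.

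Two further sentences in that section bear on the point. For secondary outcomes, "Treatment effects for the secondary outcome measures will be presented as means, SD and CIs of the means", without saying whether the means are of change or of follow-up scores. For the feasibility outcomes, "The analysis plans of the primary feasibility objectives are described in table 2".

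On timing, Table 1 marks credibility at T1 (before treatment) and T3 (1 week after), and Table 2 agrees: "All the questions will be asked at baseline and at 1 week following treatment". Satisfaction is taken once, on the "Patient Global Assessment of Treatment Satisfaction scale at 1 week following treatment". GROC has a dash at T1 and a mark at T3. The other seven secondary scales in Table 1 are marked at both times.

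**The concern.** A change score needs two measurements of the same thing on the same person. Applied as written, the definition yields nothing for most of the outcomes it names, and it sits beside a cross-reference to a table that uses other summaries. An analyst would have to decide after the fact which outcomes the sentence covers.

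Where change can be formed, there is a second question. With 20 per arm, a simple difference in change carries the baseline measurement error and responds to whatever baseline difference chance produces. The same data support an adjusted estimate that usually does better. What is at stake is the clarity and precision of the reported secondary estimates.

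**Working it through.** **1. Which outcomes can have a change score (Table 1 against the Data analysis plan)**

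- Enrolment only: willingness, acceptability of allocation, acceptability of the session, eligibility and recruitment. These lack a follow-up, and some are process counts with no between-arm contrast.
- Follow-up only: assessor blinding, contamination, adherence, satisfaction, difficulty.
- Weekly, asked of staff: acceptability of screening.
- Before treatment and at follow-up: credibility alone. Even here Table 2 plans no change score: "Mean of the total scores on the credibility scale will be computed separately for each condition", followed by a t-test.
- Secondary, T3 only: GROC. Table 3 has respondents rate improvement since enrolment, with 4 as no change: "Scores greater than 4 indicate greater improvement and scores lower than 4 indicate a perceived worsening". The T3 score is itself a change rating.
- Secondary, T1 and T3: pain interference, pain intensity, quality of life, sleep disturbance, depression, catastrophising, resilience (seven scales).

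**2. Precision for the seven scales**

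The plan gives no precision figure to reproduce. The total of 40 is 20 + 20, set by judgement, with no SD or power input.

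Inputs: n = 20 per arm (Sample size section), equal variances at T1 and T3, complete follow-up, results in SD units. The correlation r between T1 and T3 is not stated, so it is an assumption and is varied. Table 3 gives test-retest ICCs from 0.71 (pain intensity) to 0.90 (upper value for catastrophising) and none for quality of life.

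Formulae, with SE = √(2v/n):

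- change: v = 2(1 − r)
- ANCOVA: v = (1 − r²) × [1 + 1/(2n − 4)], where the small-sample factor is 1 + 1/36 = 1.028
- follow-up score alone: v = 1, so SE = √(2/20) = 0.316

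The variance ratio, ANCOVA to change, is (1 + r)/2 × 1.028. The square root gives the relative interval width.

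| r | SE change | SE ANCOVA | Variance ratio | Interval narrower by |
|---|---|---|---|---|
| 0.3 | 0.374 | 0.306 | 0.65 × 1.028 = 0.668 | 18% |
| 0.5 | 0.316 | 0.278 | 0.75 × 1.028 = 0.771 | 12% |
| 0.71 | 0.241 | 0.226 | 0.855 × 1.028 = 0.879 | 6% |
| 0.90 | 0.141 | 0.140 | 0.95 × 1.028 = 0.976 | 1% |

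A simulation of 20,000 trials at each r agreed. The empirical SEs, change against ANCOVA, were 0.318 and 0.280 at r = 0.5, 0.241 and 0.225 at 0.71, and 0.139 and 0.138 at 0.90. The gain vanishes where (1 + r)/2 × 37/36 = 1, that is at r = 72/37 − 1 = 0.946, above every ICC in Table 3.

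**3. Sensitivity to chance imbalance**

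The SD of the baseline difference between arms is √(2/20) = 0.316, about 0.32 SD. Given a baseline difference D, the change contrast shifts by D(1 − r) in favour of the arm that starts worse. For D = 0.3:

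- r = 0.5: 0.3 × 0.5 = 0.15 SD, against an SE of 0.316
- r = 0.71: 0.3 × 0.29 = 0.087, about 0.09 SD, against an SE of 0.241

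**The case against.** The strongest reply is that nothing depends on these numbers. The section itself keeps them out of sample size and progression, and the article disclaims any conclusion on effectiveness. That stands, and it sets the severity.

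Second, the feasibility outcomes measured once do have analyses, in Table 2. A reader might infer that they are left without a usable between-arm summary. They are not: the defect is that the effect-size sentence names them as well. Nor is it right that they all lack a baseline, since several are recorded at enrolment and lack a follow-up. A reader might also think GROC cannot be analysed. It can, because a difference in T3 ratings is a difference in perceived change.

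Third, calling change the noisier contrast holds only against ANCOVA. Against the follow-up score alone, change is noisier only when r is below 0.5. At the Table 3 ICCs it is more precise, with an SE 0.76 times as large at r = 0.71 and 0.45 times at 0.90.

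Fourth, the change contrast is not biased under randomisation. The shift above is conditional on a given imbalance and averages to zero over repeated randomisations.

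Fifth, the choice between change and ANCOVA is often left to an analysis plan, and none is shown. This stands in part. The article has named the change contrast, so commenting on it is fair, but it does not say whether a baseline covariate enters. If one does, the estimate equals the ANCOVA estimate and the precision point falls away.

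**Conclusion.** Two things hold. The effect-size sentence reaches further than the measurement schedule allows and does not match Table 2. And for the seven secondary scales measured twice, adjusting for baseline would narrow the interval by about 12% at r = 0.5, 6% at 0.71 and 1% at 0.90, and would largely remove the dependence on baseline imbalance.

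The sizes rest on assumptions: 20 per arm with complete data, equal variances, a linear relation, an unadjusted change contrast, and a correlation the protocol does not give. The Table 3 ICCs are reliabilities, mostly from chronic-pain samples. This trial takes pain of any duration and treats between assessments, so r could be lower and the gain larger.

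A reader might go on to infer that the credibility criterion in Table 4, or the decision to run a full trial, is put at risk. The documents do not support that: Tables 2 and 4 work with credibility scores, and the change effect sizes are barred from progression. This is a minor point of wording and reporting.

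**What to change.** Rewrite the effect-size sentence in the Data analysis plan:

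- Limit it to secondary outcomes measured at T1 and T3. For these, report the T3 between-group difference adjusted for the T1 score (ANCOVA) with its confidence interval.
- Report GROC as the between-group difference in T3 scores.
- Leave the primary feasibility outcomes, including credibility, to Table 2.

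The cost is one or two sentences. No additional data, visits or participants are needed, and the existing bar on using these figures for sample size or progression stays as it is.

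### Two feasibility outcomes called descriptive are t-tested at 20 per arm, and the only interval stated for treatment effects is that of the means, not of the between-arm difference

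*Protocol article*

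**What the plan says.** The Sample size section declines to power the study for a treatment effect and says: "Feasibility outcomes are descriptive in nature; therefore, inferential statistics regarding treatment effects will not be computed". On numbers it says: "Twenty patients will be randomly allocated to each treatment condition". The Data analysis plan likewise excludes significance levels and hypothesis tests for efficacy.

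Table 2 (Outcome measures) nevertheless assigns a t-test to two primary feasibility outcomes. For credibility, the sum of five items each scored 0–4: "Between-condition differences in creditability will be evaluated using a t-test". For satisfaction, a single item scored 0–4: "Between-condition differences will be evaluated using a t-test". Table 4 (Criteria for feasibility) judges credibility separately. It calls for modification when the control condition is more than 0.50 SD more credible than pain education, and is satisfied when the two are within 0.50 SD.

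For secondary outcomes the Data analysis plan states: "Treatment effects for the secondary outcome measures will be presented as means, SD and CIs of the means". The difference in mean scores is then to be compared with the MIC where one is available. The same section says: "Effect sizes representing between-group differences in change in the primary and secondary outcomes will be computed". It bars those effect sizes from informing the full trial's sample size or the decision to proceed.

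**The concern.** Three statements in the plan do not serve its descriptive purpose.

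- **The t-tests.** A study sized by judgement, whose authors themselves cite inadequate power, will produce p-values for credibility and satisfaction. A non-significant result is easily read as showing that the arms were equally credible or satisfying, when the study could not have shown otherwise. Credibility would also carry two yardsticks, a p-value and the 0.50 SD rule, that can point in different directions.
- **The interval.** The CI of an arm's mean describes that arm. The quantity set against the MIC is the difference between arms, and no interval is stated for it. A reader would see a point difference above or below an MIC with no sign of how imprecise it is.
- **The change score.** Effect sizes are defined as differences in change for primary and secondary outcomes alike. Many of these are measured once, so the statement cannot be carried out as written. Where a baseline exists, a change score uses it less efficiently than adjustment does.

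**Working it through.** **Inputs from the protocol article.** 20 per arm (Sample size); credibility margin 0.50 SD (Table 4); drop-out cut-points 15% and 30% (Table 4); PROMIS T-score SD 10, a normative value (Outcome measures); measurement times (Table 1).

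**Assumptions, because the document gives none.** Two-sided alpha 0.05, 95% CIs, equal SDs in the two arms.

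**The plan's own figure.** 40 rests on no alpha, power, effect size or precision target, so no formula reproduces it. Only 20 + 20 = 40 can be checked, and it agrees.

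**Step 1: the t-test at the protocol's own margin.** The standard error of a standardised difference is √(2/20) = 0.316. For a true difference of 0.50 SD the non-centrality is 0.50/0.316 = 1.58 on 38 degrees of freedom, which gives power 0.338. A difference of 0.91 SD would be needed for 80% power. For 80% power at 0.50 SD, n = 2(1.96 + 0.84)²/0.50² ≈ 63 per arm.

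**Step 2: smallest significant observed difference, and CI half-width of a between-arm difference.** Both equal t(0.975, 2n−2) × √(2/n) in SD units.

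| Per arm | Half-width (SD) | At SD 10 (T-score points) | Power at 0.50 SD |
|---|---|---|---|
| 20 | 0.64 | 6.4 | 0.34 |
| 17 (15% drop-out) | 0.70 | 7.0 | 0.29 |
| 14 (30% drop-out) | 0.78 | 7.8 | 0.25 |

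At 20 per arm, an observed credibility difference above 0.50 and below 0.64 SD in favour of the control meets Table 4's condition for modification, while the t-test reports no significant difference. An observed 0.50 SD gives t = 1.58, p = 0.12, and an approximate 95% CI of 0.50 ± 0.64, or −0.14 to 1.14 SD. The interval shows what the p-value conceals: the data would be compatible with no difference and with one about twice the margin.

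**Step 3: interval of an arm mean against interval of the difference.** For one arm the half-width is t(0.975, 19)/√20 = 2.093/4.472 = 0.47 SD, or 4.7 points at SD 10. The between-arm half-width is 0.64 SD, or 6.4 points. The stated interval is therefore narrower than the relevant one and is centred on a different quantity.

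**Step 4: which outcomes can have a change.** In Table 1, credibility is the only feasibility outcome measured both before treatment and at 1 week. Satisfaction, adherence, contamination, assessor blinding and difficulty are recorded at final assessment only. Willingness, eligibility and acceptability of allocation are recorded at enrolment only. Among secondary outcomes in that table, the global rating of change has no baseline; the others do.

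**Step 5: change score against baseline adjustment.** With equal variance σ² at both times and baseline–follow-up correlation ρ, the per-patient variance is 2σ²(1 − ρ) for change and σ²(1 − ρ²) after adjustment. The ratio of adjusted to change is (1 + ρ)/2. The document gives no ρ; over an assumed range:

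| ρ | Ratio | Variance saved |
|---|---|---|
| 0.3 | 0.65 | 35% |
| 0.5 | 0.75 | 25% |
| 0.7 | 0.85 | 15% |

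**The case against.** The strongest defence is that nothing decisive depends on these analyses. Table 4 judges credibility on the observed difference alone, satisfaction has no Table 4 criterion, and effect sizes are barred from both full-trial uses. The article says more than once that no conclusion on effectiveness can be drawn. All of this stands, and it limits the point to reporting and precision.

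Several stronger readings are tempting, and the document does not support them.

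- **That the t-tests break the plan's own ban on testing.** The exclusions cover treatment effects and efficacy. Credibility and satisfaction are feasibility outcomes, so the tests clash with the word descriptive and with the admitted low power, but do not strictly breach the ban.
- **That no between-arm difference will be shown.** Between-group effect sizes and a difference for comparison with the MIC are both planned. What is unstated is their precision. The text also does not say outright that the means are arm means, although that is the natural reading.
- **That the t-test could cause a wrong progression decision.** It appears nowhere in the progression criteria.
- **That readers will be misled by overlapping arm intervals, or by differences that exceed an MIC by chance at some known rate.** The plan does not propose judging overlap. It gives no MIC for any PROMIS scale; the only one in Table 3 is 1 point for the global rating of change. A chance rate would rest on an MIC and a trial SD that the document does not supply.

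It can also be said that a condensed article leaves interval format and covariate adjustment to an analysis plan that is not shown, and that change scores are unbiased under randomisation. Both are fair, and silence on adjustment alone would be no finding. But the article itself fixes the t-tests, the CIs of the means and the change-based effect sizes. The comment concerns those stated choices.

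**Conclusion.** The point holds as a modest one. Two outcomes described as descriptive are tested at a size that gives about 34% power at the protocol's own 0.50 SD margin, falling to about 25% at 30% drop-out. The only interval stated for treatment effects is not, on the natural reading, an interval for a treatment effect; the relevant half-width is about 0.64 SD at 20 per arm. The definition of effect sizes as differences in change cannot be applied to most primary outcomes or to the global rating of change.

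The power and half-width figures rest on an assumed two-sided 5% level, 95% intervals and equal SDs. The T-score figures also assume that the normative SD of 10 applies to patients selected for at least moderate pain, and the trial's SD may differ. The 15–35% variance saving depends on assumed correlations of 0.7 down to 0.3. No progression decision changes and the sample size of 40 is not in question. The consequence is misreading of the published results and some lost precision.

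**What to change.** - **Credibility and satisfaction:** remove the t-tests from Table 2 and report the between-arm difference with its 95% CI. Show the credibility difference in SD units beside the 0.50 SD limits of Table 4.
- **Secondary outcomes with a baseline:** report the baseline-adjusted (ANCOVA) between-arm difference with 95% CI in place of the effect size on change. Arm means and SDs can stay as description. Where an MIC is available, set the interval against it and not the point estimate alone.
- **Outcomes measured once and compared between arms, including the global rating of change:** report the simple post-treatment difference with 95% CI, and remove the reference to change for them.

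The cost is a few sentences in the Data analysis plan and Table 2 and one regression per secondary outcome with a baseline. No new data are needed, and the sample size and Table 4 criteria stay as they are.
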